## Methods: participants, interventions, and outcomes

### Study setting {9}

This is a monocentric, investigator-initiated study that will be conducted in the LVR-University-Hospital Essen, Germany, Department of Psychiatry and Psychotherapy. The LVR-University-Hospital Essen fulfills a local care mandate and is the psychiatric department of the medical faculty of the University of Duisburg-Essen. Patients are referred both regionally and trans-regionally via the Center for Treatment-Resistant Depression at LVR-University-Hospital Essen.

### Eligibility criteria {10}

Sixty patients with an MDD and 30 healthy, matched controls will be included in the study. Within the patient group, allocation to the intervention or control condition will be randomized and stratified for gender to ensure a balanced gender distribution.

The inclusion criteria are an age of 18–65 years, moderate to severe depressive episode (according to Hamilton Rating Scale for Depression, HDRS, as well as a structured clinical interview for DSM IV), and at least two different antidepressants without sufficient effect in the patient history.

The exclusion criteria include individuals under legal care and individuals in official or judicial custody, individuals with malignant diseases and/or in poor general condition, no sufficient hearing or reading ability, contraindications for TMS (that is, presence of ferromagnetic material, e.g., cochlear implants, pregnancy, cardiac pacemaker or epilepsy), previous TMS treatment, electroconvulsive therapy in the preceding 6 months, relevant structural lesions in MRI (apart from expected age-related changes such as mild cerebral microangiopathy in patients over 50 years of age or changes without expected relevance such as small arachnoid cyst), further relevant comorbidities such as substance abuse or dependence, organic mental disorders, dementia, or psychotic disorders.

In addition, the exclusion criteria relate to relevant comorbidities such as neurological disorders, e.g., multiple sclerosis, Parkinson’s syndrome, and cerebellar disease (excluding headache disorders), diseases that are associated with an inflammatory response and lead to permanently elevated inflammatory parameters and severe internal diseases that are accompanied by a significantly reduced general condition.

### Who will take informed consent? {26a}

During outpatient or inpatient treatment, potential study patients receive information about the possibility of participating in the study and are asked for permission to contact them by telephone if they are interested. In addition, interested patients who have learned about the study via the LVR-University-Hospital homepage or have received the flyer about the study via psychiatrists in a private practice can contact us via an e-mail address set up specifically for the study.

In the next step, potential participants receive further relevant information such as the time of participation and duration of the examinations via telephone. In this process, the inclusion and exclusion criteria are also systematically checked. If there are no contraindications up to this point, an appointment is made to see the investigator for an in-depth educational interview, and verbal as well as written informed consent to participate in the study is obtained.

### Additional consent provisions for collection and use of participant data and biological specimens {26b}

The participants are informed that they take part in the study voluntarily and that they can withdraw their consent to participate at any time. In addition, written consent to the collection and further processing of data in accordance with the current EU Data Protection Regulation is recorded. Since part of the data is collected in cooperation with other scientists, the participants are informed which (pseudonymized) data will be passed on to which institute and who is the responsible contact person. We will request consent for the review of participants’ medical records and for collecting blood samples to assess C395 reactive protein (CRP), interleukin (IL)-6, and tumor necrosis factor (TNF)-α, as systemic inflammatory markers will be assessed along with (epi)-genetic markers and saliva samples to target the salivary cortisol awakening response as a measure for the activity of the hypothalamic–pituitary–adrenal (HPA) axis. The participants are given the information form and a copy of the signed consent form.

Pseudonymization is realized by the ALIIAS, a software tool which implements a two-factor authenticated, de-centralized, encryption-based, deterministic pseudonymization technique to transform personal data to a pseudonym. The “full version” of the pseudonym (long ID) allows for complete re-identification (given a dedicated secret digital key owned by the “pseudonymization entity,” i.e., the individual research site). The software also provides a “human-readable” (9 characters) short ID, which is easy to link to the long ID and is compatible with most experimental procedures [26].

### Interventions

#### Explanation for the choice of comparators {6b}

In order to investigate the impact of the participants’ expectations, expectations will not be recorded retrospectively, but manipulated directly by an intervention that is described below. The treatment-as-usual condition was chosen as the control group for this study, though it must be emphasized that the term “treatment” here refers to the informed consent discussion and not the actual treatment (as explained in the “Intervention description {11a}” section).

#### Intervention description {11a}

All participants, irrespective of their assigned group, receive the same treatment with TMS within the scope of the approval. They are informed about the procedure, expected benefits, and risks. Compared to a standard briefing from a medical professional, this intervention contains more detailed and more encouraging information prior to the treatment with TMS. With this goal in mind, a separate educational sheet was designed to emphasize the promising nature of the treatment, without withholding relevant information about the risks and side effects from the participants. In this way, the intervention targets the patient’s educational process while still in the preparatory phase of an approved and established therapy. Half of the study participants (intervention group), however, receive additional information emphasizing the promising character of the therapy as well as the safety of the method. Here, we use visual material about the device, illustrations from studies that were able to prove the effectiveness of TMS and a more appealing presentation. Furthermore, an information film about TMS is presented in the intervention group only. Patients are not aware that two different types of informed consent discussions are being used.

#### Criteria for discontinuing or modifying allocated interventions {11b}

Overall, the study is at a very low risk for potential harm. No harm is expected from the intervention in the form of modified patient education about the approved therapy with TMS. Prior to the start of the study, study participants will be asked to indicate whether they would like to be informed of incidental findings in addition to this education.

The discontinuation criteria for individual participants are the occurrence of intolerable and/or unexpected undesirable side effects during the therapy with TMS, the occurrence of the exclusion criteria during the course of the therapy, violation of the study protocol, and other circumstances that would endanger the health of the participant if he or she continued to participate in the study, as well as on participant request. Change of medication during the treatment is not an exclusion criterion per se but will be recorded as an event that will need additional control.

#### Strategies to improve adherence to interventions {11c}

Participation in the study offers patients the option of treatment with TMS, which is not yet routinely available at all clinical sites in Germany and which will also be offered independently of study participation in the inpatient setting. In the outpatient setting, however, treatment costs have not always been covered by health insurance in Germany up to now, so that participation in the study may enable patients to choose a more preferable form of treatment. In addition, very extensive psychometric testing is performed, which goes beyond the standard clinical practice and can provide patients with an indication of their current level of performance. Adherence, in the present study, consists of daily attendance at the clinic where TMS is performed, which can be tracked very easily.

As therapy adherence is certainly a major challenge in the study, and in order to take quality control into account, the complexity of the protocol will already be addressed during the first telephone contact, so that the participants can adjust accordingly. In the event that at this point there is already strong uncertainty regarding the realization of the study visits, the participants will be informed about alternative treatment options for depression which would be easier to implement.

#### Relevant concomitant care permitted or prohibited during the trial {11d}

The aim is to ensure that during study participation, any existing drug and/or psychotherapeutic treatment is continued with as little change as possible. In the event of a relevant change during study participation, discontinuation must be discussed individually. Change of medication during the treatment is also not an exclusion criterion per se but will be recorded as an event that will need additional control.

#### Provisions for post-trial care {30}

The possible disadvantages (risks, impairments, burdens) for the study participants resulting from the planned examinations with MRI, blood sampling, and collection of saliva samples are negligible compared to the expected benefit. The expected risks of blood sampling are minor pain and possibly a small hematoma at the puncture site. The immediate benefit for the study participants is the possibility of an optimization of the therapy effect; in the long term, the study could mean an improvement in treatment practice. Overall, the study involves a very low risk for potential harm. No harm is expected from the intervention in the form of modified education about the approved therapy with TMS. In principle, participants will be offered the full range of depression treatment services at LVR-University-Hospital Essen as an alternative to study participation or as a future treatment option.

### Outcomes {12}

#### Primary outcomes

Psychometric tests to assess therapy success: The tests will be administered at four points in time (T1: before therapy, T2: in week 2 of therapy, T3: in week 3 of therapy, T4: after therapy). T1 was defined as the examination within a period of 2 weeks before the start of therapy, and T4 as the examination within a period of 2 weeks after the end of therapy.

The following tests are used, some of which are questionnaires to be completed by the patient and some of which record the clinical examiner’s impression.

Beck Depression Inventory-II (BDI-II): This instrument measures the severity of depressive symptoms. In the form of a questionnaire, the patient self-reports how pronounced certain symptoms were during the previous week [27].

Montgomery Asberg Depression Scale [MADRS [28]]: In contrast to the BDI-II, MADRS is an instrument for third-party assessment of the severity of a depressive episode. The questionnaire is completed by the patient’s clinical practitioner as part of the usual clinical routine or by a clinical psychologist, who is blinded to intervention allocation.

Clinical Global Impression severity scale (CGI): This is a brief third-party assessment of the severity of illness by the examiner [29, 30], who is blinded to intervention allocation.

Snaith-Hamilton Pleasure Scale: This questionnaire is used to measure subjectively experienced joylessness (anhedonia) in psychiatric patients [31, 32].

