### Trial design {8}

We are planning an interventional, monocentric, randomized, controlled trial with two MDD patient groups of 30 participants each.

Our study is of the parallel group type, i.e., we are looking at two groups of patients in parallel, with one group of patients receiving an intervention while the other one does not. The framework is “superiority”: we expect to see superiority in outcome parameters in the intervention group. The allocation ratio in the intervention versus the control group is 30:30.

As it is to be expected that about 10% of the data will be lost due to the complex study protocol with several examinations at a total of four time points, at least 35 patients should be recruited per group. This minimum recruitment number seems achievable based on our experience with previous studies. The details of the intervention are outlined below.

In addition, an age-, sex-, and education-matched control group of 30 participants will be recruited, who will serve as a control only for the additional experimental investigations, which is the MRI part and the eyeblink conditioning. In these two subprojects, the first step is to evaluate the changes in the context of depressive illness in general compared to a healthy control group, see the “Outcomes {12}” section.

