## Statistical methods

### Statistical methods for primary and secondary outcomes {20a}

Analysis of variance (ANOVA) with repeated measures is planned for the evaluation of the parameters of therapy outcome (questionnaires for depression), therapy expectancy (questionnaires see above), biological parameters, and tests for cerebellar function (neurological examination, ataxia scores, and blink reflex conditioning). In case of missing values, a linear mixed model analysis is planned. An unpaired *T*-test or chi-square test is planned to determine the group differences at a given point in time. Correlation analyses are planned to correlate parameters of therapy success with treatment expectations.

The MRI data will be analyzed using statistical parametric mapping (SPM, https://www.fil.ion.ucl.ac.uk/spm/; last access 8/15/2023): automated group comparisons in terms of *T*-test and ANOVA will be performed including covariates.

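### Four unranked depression scales are all primary, and no scale, visit, model term or any/all rule decides the superiority claim

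*Protocol article*

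**What the plan says.** Under Outcomes {12}, Primary outcomes, the article introduces the set with "Psychometric tests to assess therapy success: The tests will be administered at four points in time" (T1 before therapy, T2 and T3 during it, T4 after it). It then lists four instruments with equal standing:

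- "Beck Depression Inventory-II (BDI-II): This instrument measures the severity of depressive symptoms" (self-rated).
- "MADRS is an instrument for third-party assessment of the severity of a depressive episode" (rated by the patient's clinical practitioner or a clinical psychologist).
- "Clinical Global Impression severity scale (CGI): This is a brief third-party assessment of the severity of illness by the examiner".
- "Snaith-Hamilton Pleasure Scale: This questionnaire is used to measure subjectively experienced joylessness (anhedonia) in psychiatric patients".

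Trial design {8} sets a superiority framework and adds: "we expect to see superiority in outcome parameters in the intervention group". The plural is not resolved into one, any or all.

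Statistical methods {20a} states: "Analysis of variance (ANOVA) with repeated measures is planned for the evaluation of the parameters of therapy outcome (questionnaires for depression". It does not say whether the group term or the group-by-time term answers the question. It then adds an unpaired t-test "or chi-square test is planned to determine the group differences at a given point in time", without naming the point in time or the variables. Sample size {14} gives alpha as 0.05. No other section gives a significance level.

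**The concern.** A superiority trial needs one rule, fixed in advance, that turns the data into a yes or a no. Here the main hypothesis (better therapy success through higher expectation) could be answered by any of four scales. For each scale the answer could come from either ANOVA term or possibly from a single visit. If the scales disagree, the document does not say whether the trial succeeded.

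Other sections do not settle it. Objectives {7} describes therapy success as psychometric tests and cognitive tasks together. Sample size {14} draws on effect sizes from five instruments of a cited study. Two of these (the Hamilton scale and the WHO-5) are not primary here, and MADRS is not among the five.

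The Discussion itself names the low case number as a weakness. With about 30 analysed patients per group, one significant result among several eligible ones would not serve as confirmation.

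**Working it through.** **The plan's own figure.** The article states no familywise error rate, so there is none to reproduce. Its one calculated number is n = 7 per group (alpha 0.05, power 0.95, four time points, two groups, d from 0.79). I checked whether this reveals the intended term, using noncentral-F power with f = d/2, m = 4 and an assumed visit correlation ρ.

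- Group-by-time: λ = N·m·f²/(1−ρ). With d = 0.79, f = 0.395, N = 14 and ρ = 0.5, λ = 14 × 4 × 0.156 / 0.5 ≈ 17.5. Power is 92.9%, and 8 per group are needed for 95%.
- Group main effect: λ = N·m·f²/(1+(m−1)ρ). With d = 0.79 and ρ = 0.5, 28 per group are needed. With d = 1.6, 6 to 8 are needed (ρ = 0.3 to 0.5).

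A figure near 7 can therefore come from either term, depending on d and ρ. The calculation does not identify the deciding test. It also has no bearing on the multiplicity figures below.

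**Inputs for the error rate.**
- From the document: four primary scales, 30 per group, T1–T4, alpha 0.05, no interim analysis.
- Assumed: two-sided tests; correlation between scales 0.3–0.8; correlation between visits 0.5–0.7; no true effect; success declared if any eligible test reaches p < 0.05; the ANOVA sentence covers all four scales.

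**Independence bound.** For k independent tests the error rate is 1 − 0.95^k. For k = 4 this is 1 − 0.8145 = 18.5%. Scales measured in the same patients are positively correlated, so the rate was simulated.

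**Simulated chance of at least one false positive.** Ranges reflect visit correlation 0.5–0.7 and simulation error.

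| Scale correlation | One test per scale (4 tests) | Group and group-by-time terms (8) | t-tests at T2, T3, T4 (12) | Both ANOVA terms and t-tests (20) |
|---|---|---|---|---|
| 0.3 | 18% | 32% | 35–40% | 45–48% |
| 0.5 | 16% | 29% | 32–36% | 41–44% |
| 0.7 | 13% | 24–25% | 27–31% | 35–38% |
| 0.8 | 12% | 22% | 24–27% | 31–33% |

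T1 precedes therapy and is not counted as an efficacy test, so the largest family is 4 × (2 + 3) = 20.

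In multiples of 5%:
- One test per scale: 12/5 = 2.4 to 18/5 = 3.6.
- Both ANOVA terms: 22/5 = 4.4 to 32/5 = 6.4.
- All 20 tests: 31/5 = 6.2 to 48/5 = 9.6.

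**Cost of control.** A comparison with 80% power at two-sided 0.05 (58 degrees of freedom) has noncentrality 2.85. At alpha 0.0125 the same effect has power of about 61%. In normal approximation, the d detectable with 80% power at 30 per group rises from (1.960 + 0.842)·√(2/30) ≈ 0.72 to (2.498 + 0.842)·√(2/30) ≈ 0.86.

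**The case against.** The strongest reply is that much of the inflation depends on things the article does not say. Most of that reply is right.

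- **Unadjusted 5% testing.** A reader might infer that every scale is tested at 5% without adjustment. The article does not say so. The 0.05 belongs to the sample-size calculation, and an adjustment could stand in an analysis plan that is not shown.
- **A 16-test grid.** A reader might multiply four scales by four visits. That counts T1, which cannot show therapy success. The sentence on t-tests and chi-square tests names neither the primary scales nor the visits, and the chi-square test fits baseline comparisons as well. It is vague, and it does not prescribe visit-wise tests of every scale. The repeated-measures ANOVA, which the article does assign to the depression questionnaires, covers all visits in one test per term.
- **A nine-fold error rate.** This needs every post-baseline t-test and both ANOVA terms on all four scales, an any-hit rule, and scale correlations at the low end of the assumed range.
- **The success rule.** If all four scales had to be positive, the error rate would not be inflated. The cost would be power.

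One part of the concern is untouched. Which outcome decides the trial is a protocol matter, and the article is not silent on it: it gives primary status to four scales. A later plan that picked one would be changing the protocol's statement.

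**Conclusion.** The point stands as a defect in how the primary outcome is fixed. Four scales share primary status, and no scale, visit, model term or any/all rule settles the superiority claim. This follows from the text and needs no assumption.

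The size of the error is conditional. It requires that any one scale suffices and that each eligible test is run at 5%. With one test per scale, the false-positive rate is then about 12–18% for scale correlations of 0.3–0.8, or roughly two to four times nominal. The higher figures, about 22–32% with both ANOVA terms and about 31–48% with the visit-wise tests as well, show how far the wording could stretch. They do not describe what the article commits to. The point should be settled before analysis, because it changes what the trial can conclude.

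**What to change.** Before outcome data are seen by group, amend the protocol and the registry entry through the route in the section on protocol amendments {25}, in one of two ways.

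1. **One primary endpoint.** Name one scale and one contrast, for example the group difference in MADRS at T4 adjusted for T1, using the ratings the protocol already collects. The MADRS may be completed by either the clinical practitioner or a clinical psychologist, so restricting the endpoint to one type of rater could leave patients without a score. Make the other three scales secondary and label T2 and T3 comparisons descriptive.
2. **Four primaries under control.** Keep all four scales, prespecify one test per scale, and claim superiority only for scales that pass Holm across those four tests.

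Both options change wording only and need no new data. Under the first, three scales lose primary status. Under the second, the first-step alpha is 0.05/4 = 0.0125, with the loss of power shown in the working (80% to about 61% on one scale).

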### Assignment of interventions: blinding

#### Who will be blinded {17a}

This is a double-blinded study, i.e., the participants do not know which group they were assigned to, nor that an intervention takes place during the educational process. Since the investigator performs the medical consultation, which at the same time is the intervention, blinding is not possible here. The additional scientific staff who survey the outcomes (i.e., eyeblink conditioning and cognitive tasks) are blinded regarding the intervention group during the entire course of the study. As the therapist factor should not be underestimated, the protocol is realized in a way that all the patients interact with the same therapist for each respective procedure (the same person performing the psychological tests and interviews, the same person applying the TMS treatment, and the same person communicating regarding the informed consent).

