### Oversight and monitoring

#### Composition of the coordinating center and trial steering committee {5d}

This is a monocentric, investigator-initiated study. The coordinating center is the LVR-University-Hospital Essen. The daily local organization and coordination of the study are ensured by [name] [name] (KMS), who obtains informed consent as the clinic’s physician. [name]. [name] (KK) and [name]. [name] (DT) supervise the study. Meetings are held regularly every 3 months as part of the in-house research conference and at short notice to clarify questions and problems that may arise. There is no Stakeholder and Public Involvement Group (SPIG).

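### MADRS, a primary outcome, has two permitted rater types: this conflicts with the same-person rule in {17a} and leaves one rater's blinding unsecured

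*Protocol article*

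**What the plan says.** **Who rates MADRS.** In the protocol article, Outcomes {12}, Primary outcomes, MADRS is one of four instruments listed as psychometric tests of therapy success. On timing: "The tests will be administered at four points in time (T1: before therapy, T2: in week 2 of therapy, T3: in week 3", with T4 after therapy. The rater is the patient's "clinical practitioner as part of the usual clinical routine or by a clinical psychologist, who is blinded to intervention allocation". The article gives no rule on which of the two rates which patient or visit.

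**Who rates CGI.** The neighbouring entry has a single rater: "This is a brief third-party assessment of the severity of illness by the examiner [29, 30], who is blinded to intervention allocation".

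**Blinding, {17a}.** The section opens: "This is a double-blinded study, i.e., the participants do not know which group they were assigned to". It then discloses an exception: "Since the investigator performs the medical consultation, which at the same time is the intervention, blinding is not possible here". On outcome staff it says: "The additional scientific staff who survey the outcomes (i.e., eyeblink conditioning and cognitive tasks) are blinded". Depression raters are not mentioned.

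**Same-person rule, {17a}.** Because the therapist factor is thought important, every patient is to meet the same individual for each procedure, including "the same person performing the psychological tests and interviews".

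**Who holds the consent discussion, {5d}.** A physician of the clinic, who also coordinates the study from day to day, obtains consent. Under {17a} the consultation is itself the intervention.

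**The concern.** Two things do not fit.

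First, {12} offers two kinds of MADRS rater where {17a} promises one person. {17a} gives a reason for that promise, and {12} undoes it for a primary outcome.

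Second, only the psychologist's blinding is clearly stated. The clause is singular and directly follows that role. Nothing else in the article says that the practitioner is unaware of the allocation or is a different person from the one who held the consultation.

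This matters more than usual in a trial of expectation. BDI-II and the Snaith-Hamilton scale are self-reports from patients whose expectations one arm sets out to raise. MADRS and CGI are the two primary instruments that do not depend on the patient's own report. A MADRS rater who knew which consultation was given could bring an expectation of their own into the score. The sample size section and the discussion both allow that the true effect may be small, so a modest rating bias could be mistaken for it. A change of rater within a patient would also add noise to the change over time.

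**Working it through.** The article gives no figure on this point, so there is none to reproduce. The check is a comparison of sections, followed by a sensitivity illustration.

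**Step 1: number of raters**

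| Section | Rule |
|---|---|
| {12}, MADRS | Patient's practitioner in routine care, or a psychologist |
| {12}, CGI | One examiner |
| {17a} | One individual for psychological tests and interviews, all patients |

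{12} itself classes MADRS among the psychometric tests, so it cannot easily be placed outside the {17a} rule. The practitioner is defined patient by patient, and {26a} recruits from inpatient care, outpatient care and private-practice referral. That route is therefore unlikely to lead to one individual for everyone. The two sections cannot both hold as written.

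**Step 2: who is stated to be blinded**

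| Rater | Stated blinded? | Where |
|---|---|---|
| CGI examiner | Yes | {12} |
| MADRS psychologist | Yes | {12} |
| MADRS practitioner | Only if the clause is read as covering both roles | {12} |
| Eyeblink and cognitive-task staff | Yes | {17a} |
| Investigator holding the consultation | No, disclosed | {17a} |

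The list in {17a} is introduced with i.e., so it reads as a definition rather than as examples. The practitioner is the one rater of a primary outcome whose status is open.

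**Step 3: illustration of bias (all shifts assumed)**

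Inputs: 30 per group ({14}); alpha 0.05 ({14}), taken as two-sided; no true effect; a normal approximation for a two-group comparison at one time point. Let b be the difference between arms in mean rating error, in SD units. An error equal in both arms cancels, so only the difference counts.

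Noncentrality: δ = b / √(2/30) = b × √15 = 3.873 b.

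Rejection rate: 1 − Φ(1.96 − δ) + Φ(−1.96 − δ).

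| b (SD) | δ | Type I error |
|---|---|---|
| 0 | 0 | 5.0% |
| 0.10 | 0.39 | 6.7% |
| 0.15 | 0.58 | 8.9% |
| 0.20 | 0.77 | 12.1% |
| 0.30 | 1.16 | 21.3% |

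The 0.15 row also represents a 0.3 SD shift that affects half of the ratings: 0.3 × 0.5 = 0.15.

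**Step 4: illustration of noise (assumed)**

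At 30 per group the difference detectable with 80% power is (1.960 + 0.842) × √(2/30) = 0.72 SD. If mixed raters add 10%, 20% or 30% to the score variance, power at that difference falls to 76%, 73% or 69%.

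**The case against.** The other side has a good deal to say, and most of it limits the point.

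- **Unblinded rating is nowhere stated.** The blinding clause closes a sentence that names both raters and can be read as covering both. This stands: the text leaves the matter open and does not admit a breach.
- **A reader might infer that the consenting physician, or colleagues who know the allocation, score MADRS.** {5d} does not show that. It says who obtains consent and coordinates. Other sections point the other way: the sequence is password-protected ({16b}), the investigator opens each envelope just before the intervention ({16c}), and patients do not know that two kinds of consultation exist ({11a}). What remains is an overlap of roles that no section rules out.
- **A reader might infer that raters change between T1 and T4.** That is not stated either. The choice could be split by setting, with one rater per patient. Even so, patients would then have different raters, which {17a} excludes.
- **A reader might call the double-blind label false.** {17a} openly says that the consulting investigator is not blinded, so nobody is misled on that. The open question concerns outcome assessment only.
- **Blinding of depression raters is partly covered.** {12} already states it for the CGI examiner and the MADRS psychologist, and the gap in {17a} should be read with that in mind.
- **The full protocol may assign raters.** It may. But the article states an either/or rule in one section and a single-person rule in another. That is a conflict in what is written, not a detail left out.

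**Conclusion.** The point holds in a limited form and should be corrected. {12} and {17a} disagree on how many people rate MADRS, and the blinding of one permitted rater is not secured. The conflict rests on the text alone.

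The size of any bias cannot be derived from the documents. The 9% to 21% range rests on an assumed between-arm shift of 0.15 to 0.3 SD, applies to the MADRS comparison alone, and uses a one-time-point approximation rather than the planned repeated-measures ANOVA. It shows how sensitive 30 per group is to rating bias. It does not estimate the trial's actual error rate, and a reader should not take 21% as a finding. The power figures are equally conditional on assumed rater variance.

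Two extensions are not supported. CGI is already stated to be rated blind and needs no new rater. Nothing in the article gives grounds to require blinding of the person who applies TMS.

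**What to change.** **In {12}:** state that the trial analysis uses only MADRS ratings made by the blinded clinical psychologist, the same person at T1 to T4, as {17a} already promises. Flag any practitioner ratings already collected and use them only in a sensitivity analysis.

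**In {17a}:** list the MADRS and CGI raters among the blinded staff, state that the person who delivers the consultation rates no outcomes, and describe the trial as participant- and assessor-blinded.

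**Cost:** mainly wording, and the psychologist is a role the article already names. Three costs should be acknowledged.

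- A routine rating can no longer stand in for a missed psychologist rating. The mixed model planned in {20a} and {20c} would handle that visit as missing.
- The psychologist must cover up to 60 × 4 = 240 ratings, or 70 × 4 = 280 if 35 per group are recruited. The article does not give the available capacity.
- Recruitment began in June 2022 and was to finish by November 2023 (Trial status), so some patients may have only practitioner ratings. The main analysis would lose those MADRS values, and the sensitivity analysis would show whether that matters.
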